### Data collection and management

2.8

We will code the identification of patients. We will also enter data collected at each study visit into a paper case report form (CRF) with double data entry. Outcome data entered into the database will be verified against the source data on the paper CRFs. We will encourage patients to complete study and follow-up using text messages and personal calls.

### Sample size calculation

2.9

This clinical study using human biological material is an exploratory study. Therefore, we have performed no effect size-based statistical calculation of the number of study participants. Considering the dropout rate, we aim to recruit 100 study participants from the Dongguk University Ilsan Oriental Hospital.

### Statistical analysis

2.10

A basic analysis of the study results will compare the difference in evaluation indicators of groups I and II (with circulatory disturbances) with that of group III (without circulatory disturbances) at visit 1. All statistical analyses will be subjected to two-tailed tests, and the significance level will be set at 5%. A descriptive analysis of the evaluation items and blood indices for each group will be conducted to represent the categorical variables as n (%) and continuous variables as mean ± standard deviation. To compare the intergroup differences for the obtained outcome value for each item, categorical variables will be subjected to the chi-square test and Fisher exact test, whereas continuous variables will be analyzed using the *t* test and analysis of variance or nonparametric methods such as Mann-Whitney *U* test and Kruskal-Wallis test for those not meeting the normality criteria. Analysis of covariance will be performed when it is necessary to control underlying variables, such as demographic variables (sex, age, weight, and height). For data with a missing value, the last observation carried forward will be used through CRF inspection to replace the missing value.

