### Study aims

2.1

This exploratory study is aimed at designing a Korean medicine diagnostic technique for metabolic diseases with blood stasis, particularly circulatory disturbances, to explore the related Korean medicine treatment options and evaluate their validity by analyzing clinical data and blood samples.

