#### Inclusion criteria

2.4.1

We will include patients who are eligible according to the following criteria:

1.Individuals aged between 20 and 70 years.2.Individuals who voluntarily sign the informed consent form for the clinical study, or those who are incapable of providing voluntary agreement but whose legal representatives sign the informed consent form.3.Individuals who are willing to cooperate and comply with regulations during the study period.4.Individuals who consent for blood collection for the purpose of this study.

For the study participants who meet the aforementioned criteria, the selection criteria for each group are as follows:

1.Ankle–brachial index (ABI) <0.9 or triglycerides ≥150 mg/dL and high-density lipoprotein cholesterol <40 mg/dL in men and <50 mg/dL in women2.Blood stasis score (≥9 points out of 32 total points)Group I (circulatory disturbance I): Meets both aforementioned criteria (1 and 2).Group II (circulatory disturbance II): Meets one of the aforementioned criteria (1 but not 2).Group III (normal): Does not meet either criterion from the aforementioned criteria.

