#### Primary outcome

2.7.1

1.Resistin, serum amyloid P component, C-reactive protein, and D-dimer are the candidate indicators that seem effective in diagnosing blood stasis based on previous studies on blood stasis.^[12–15]^2.Blood stasis score: A blood stasis questionnaire used to assess the presence/absence of blood stasis and to evaluate the blood stasis score was developed by the Korea Institute of Oriental Medicine through a blood stasis diagnosis technique development research project.^[16–18]^ It was executed for 5 years from 2013 to 2018, and it showed high reliability and validity.^[17,18]^ We extracted 31 questions related to metabolic disorders from the blood stasis questionnaire using the experts’ delphi method and validity analysis, in order to use it as an assessment tool in this study.^[19]^ By referring to the standard operating procedure of each question, a Korean medicine doctor will directly interview each patient and complete the blood stasis questionnaire (Supplemental Digital Content (Appendix 1)).

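### The only contrast named in section 2.10, Groups I and II against Group III, does not isolate blood stasis; Group I versus Group II should be named for the four blood markers

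*Protocol article*

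**What the plan says.** Section 2.4.1 builds three groups from two criteria. Criterion 1 is a low ABI or a lipid pattern. Criterion 2 is "Blood stasis score (≥9 points out of 32 total points"). The three definitions read as follows.

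- Both features present: "Group I (circulatory disturbance I): Meets both aforementioned criteria (1 and 2").
- Criterion 1 alone: "Group II (circulatory disturbance II): Meets one of the aforementioned criteria (1 but not 2").
- Neither feature present: "Group III (normal): Does not meet either criterion from the aforementioned criteria".

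Section 2.7.1 lists four blood markers (resistin, serum amyloid P component, C-reactive protein, D-dimer) as "candidate indicators that seem effective in diagnosing blood stasis based on previous studies on blood stasis". Section 2.1 gives the aim as "designing a Korean medicine diagnostic technique for metabolic diseases with blood stasis", and the sentence goes on to single out circulatory disturbances.

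Section 2.10 sets out its basic analysis as follows: "evaluation indicators of groups I and II (with circulatory disturbances) with that of group III (without circulatory disturbances) at visit 1". It then lists t test and ANOVA, or Mann-Whitney and Kruskal-Wallis, for differences between groups, and ANCOVA where demographic variables need control. It names no comparison of Group I with Group II.

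**The concern.** The markers are proposed as indicators of blood stasis, but the named contrast is defined, in the protocol's own labels, by the presence or absence of circulatory disturbance. Group II falls below the stasis cut-off by definition, yet it sits on the affected side. A difference in C-reactive protein or D-dimer between Groups I and II and Group III could arise wholly from low ABI or dyslipidaemia, and this contrast gives no way to tell.

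What is at stake is attribution. The Discussion expects the study to provide a basis for later clinical trials, so a marker credited to stasis on this comparison could be carried forward on the wrong grounds.

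**Working it through.** **Step 1: what each contrast varies** (from the definitions in section 2.4.1)

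| Contrast | Criterion 1 differs? | Stasis criterion differs? |
|---|---|---|
| I and II pooled vs III | yes | partly (Group I only) |
| I vs III | yes | yes |
| II vs III | yes | no |
| I vs II | no | yes |

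Only the last row varies stasis with criterion 1 held fixed. This needs no assumption about numbers.

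**Step 2: inputs for an illustration.** The documents give a recruitment target of 100 (section 2.9) and two-sided tests at 5% (section 2.10). They give no power, effect size, SD, dropout rate or group sizes, so there is no figure to reproduce. Assumed: all 100 analysed, groups of 33/33/34, SD 1, and a shift d of 0.5, 0.7 or 0.8. A metabolic-only marker has means (d, d, 0) in Groups I, II and III. A stasis-only marker has means (d, 0, 0).

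**Step 3: formula.** Two-sample t test with noncentrality δ = d × √(n_a n_b / (n_a + n_b)) and n_a + n_b − 2 degrees of freedom. Power is the probability that the noncentral t exceeds the two-sided 5% critical value in absolute terms.

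- Pooled, 66 vs 34: √(66 × 34 / 100) = 4.737.
- I vs II, 33 vs 33: √(33 × 33 / 66) = 4.062.
- I vs III, 33 vs 34: √(33 × 34 / 67) = 4.092.
- In the pooled contrast a stasis-only shift shrinks to d × 33/66 = d/2.

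At d = 0.7:

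- metabolic-only, pooled: δ = 0.7 × 4.737 = 3.32, flagged 91%
- stasis-only, pooled: δ = 0.35 × 4.737 = 1.66, power 38%
- stasis-only, I vs II: δ = 0.7 × 4.062 = 2.84, power 80%
- stasis-only, I vs III: δ = 0.7 × 4.092 = 2.86, power 81%

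| Probability of p < 0.05 | d = 0.5 | d = 0.7 | d = 0.8 |
|---|---|---|---|
| Metabolic-only marker, pooled vs III | 65% | 91% | 96% |
| Stasis-only marker, pooled vs III | 22% | 38% | 47% |
| Stasis-only marker, I vs II | 52% | 80% | 89% |

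In I vs II a metabolic-only marker has no true difference, so it is flagged at about 5%.

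The pooled stasis figures ignore the extra spread from mixing shifted and unshifted people. Simulation (10,000 runs) that includes it gives 20% and 42% at d = 0.5 and 0.8, so the table is slightly generous to pooling.

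**Step 4: other splits.** Five splits were tried with a normal approximation, which runs a point or so above the t-based values: 33/33/34, 25/25/50, 40/40/20, 20/50/30 and 50/20/30.

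| Range over splits | d = 0.5 | d = 0.8 |
|---|---|---|
| Metabolic-only, pooled | 52–71% | 89–98% |
| Stasis-only, pooled | 10–37% | 18–75% |
| Stasis-only, I vs II | 42–61% | 81–95% |

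Within every split, I vs II has more power for a stasis-only marker than the pooled contrast.

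**Step 5: each group against Group III.** In I vs III a stasis-only marker keeps its power (81% at d = 0.7). A metabolic-only marker with the same shift is flagged equally often, because the two groups differ on both criteria. II vs III contains no stasis difference, so a stasis-only marker is flagged there at about 5%. Finding one comparison significant and the other not is no test of I against II.

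**Step 6: the omnibus test.** In simulation at 33/33/34, three-group ANOVA flags a metabolic-only marker in 54% and 92% of runs (d = 0.5, 0.8) and a stasis-only marker in 53% and 92%. A significant omnibus result does not tell them apart.

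**The case against.** Several points on the other side stand.

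- **The aim includes circulatory disturbance.** Section 2.1 singles it out, and two of the groups are named for it. A reader might infer that the named comparison cannot answer the study's question at all. The documents do not support that: it addresses one part of the aim and leaves stasis unseparated.
- **Group I versus Group II is not excluded.** Section 2.10 calls the comparison a basic analysis, not a primary one, and lists three-group tests. Pairwise follow-up may be set out in an analysis plan that is not shown. The point is therefore not that detail is missing. It is that the one contrast the article does name does not match the stated purpose of the markers.
- **A true stasis marker need not be missed.** A reader might infer that it would be. Loss of power occurs only if Groups I and II are pooled, and even then the signal is diluted, not absent. With each group set against Group III, the remaining problem is confounding.
- **The figures are illustrative.** Group sizes and effects are assumed. The direction follows from the definitions, but the percentages do not come from the protocol.
- **The study is exploratory.** Section 2.9 says so, and that excuses the absence of a power calculation. It does not make a difference defined by criterion 1 attributable to stasis.

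**Conclusion.** The concern holds in a limited form. Under either reading of the sentence in section 2.10, a marker difference cannot be attributed to blood stasis. If the groups are pooled, a marker tied only to ABI or lipids can be significant and a stasis-only marker loses roughly half its power: 38% against 80% at d = 0.7, assuming 33/33/34 and SD 1. If each group is compared with Group III, power is kept but stasis is confounded with criterion 1.

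The structural part rests only on the group definitions; the percentages rest on the assumed sizes and shifts. One limit remains. No group meets criterion 2 without criterion 1, so I versus II estimates the stasis difference only among people with circulatory disturbance. That population fits the stated aim.

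**What to change.** In section 2.10, name Group I versus Group II as the main contrast for the four blood markers, and report each as a difference with a 95% CI. Keep the comparison with Group III as the supporting contrast for circulatory disturbance, and say whether Groups I and II are pooled there or compared separately. The new contrast concerns the blood markers only: the blood stasis score defines the split between Groups I and II, so a difference in it is built in.

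The cost is a change of wording, with no new participants, visits or assays. The downside is that the main contrast uses only participants in Groups I and II, about 66 of 100 under the equal split assumed above.

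A multiplicity adjustment such as Holm over the four markers is optional in this exploratory study and not part of the fix. If it is adopted, its first step (0.05 / 4 = 0.0125) would lower the 80% at d = 0.7 to about 61%.

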## Discussion

3

This prospective observational study is designed to investigate the effectiveness of the diagnosis index for metabolic diseases with blood stasis by analyzing clinical data. Treating blood stasis is effective in treating metabolic diseases in traditional Korean medicine,^[8,11]^ but there is insufficient evidence regarding the effectiveness of the diagnosis index in metabolic diseases with blood stasis. Findings of this study will provide a summary of the current state of evidence regarding the effectiveness of the diagnosis index in managing metabolic diseases with blood stasis. In addition, this study is expected to provide a basis for clinical trials to confirm the efficacy of Korean medicine for treatments of metabolic diseases with blood stasis.

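### The aim is diagnostic, but the described analysis tests group differences only: no discrimination measure is named, and the one named contrast does not isolate blood stasis

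*Protocol article*

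**What the plan says.** Section 2.1 of the Protocol article gives the purpose as "designing a Korean medicine diagnostic technique for metabolic diseases with blood stasis". The Discussion restates it: the study is to "investigate the effectiveness of the diagnosis index for metabolic diseases with blood stasis by analyzing clinical data". Under Primary outcome (2.7.1), resistin, serum amyloid P component, C-reactive protein and D-dimer are listed because they "are the candidate indicators that seem effective in diagnosing blood stasis based on previous studies on blood stasis". The blood stasis score is listed beside them.

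The groups are defined in 2.4.1 by two criteria. Criterion 1 is a low ABI or an adverse lipid profile. Criterion 2 is "Blood stasis score (≥9 points out of 32 total points"). The first group is "Group I (circulatory disturbance I): Meets both aforementioned criteria (1 and 2"). Group II meets criterion 1 but not 2, and group III meets neither.

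Section 2.10 names one contrast at visit 1, groups I and II against group III. The methods it lists "To compare the intergroup differences for the obtained outcome value for each item" are chi-square and Fisher tests, t test and ANOVA, Mann-Whitney and Kruskal-Wallis, with ANCOVA where adjustment is needed. Descriptive summaries are given by group. Testing is two-sided at 5%. Section 2.9 sets the target at 100 in total, with no effect-size calculation and no group sizes.

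**The concern.** A diagnostic question asks how well a marker separates people with the condition from people without it. The natural answers are an AUC, or sensitivity and specificity at a cut-off, each with an interval. Section 2.10 asks whether group averages differ, which is a weaker question.

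Two features of the plan widen the gap. First, the score is a multi-point scale and a primary outcome, yet in the described analysis it meets the biomarkers only as a yes/no split at 9, so information is lost. Second, the named contrast puts group II, who are stasis-negative by definition, on the disease side. It therefore sorts participants by criterion 1.

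If the analysis is carried out as described, the study could end with p-values for group differences and no reported estimate of how well any of the four indicators identifies blood stasis. A marker of ABI or lipid status could also be taken for a marker of stasis.

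**Working it through.** **1. What the named contrast separates (definitions in 2.4.1).**

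| Group | Criterion 1 (ABI/lipids) | Criterion 2 (score ≥9) |
|---|---|---|
| I | yes | yes |
| II | yes | no |
| III | no | no |

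Pooling I and II against III makes criterion 1 the dividing line. If each of I and II is instead compared with III, I vs III differs on both criteria and II vs III on criterion 1 only. Only I vs II varies blood stasis with criterion 1 held fixed, and 2.10 does not name that contrast.

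**2. What a just-significant difference means for discrimination.** The article gives 100 in total and alpha 0.05 two-sided. It has no figure of its own to reproduce here. Group sizes are my assumption. The conversions assume normal markers with equal variance:

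- d at p = 0.05: t(0.975, n1+n2−2) × √(1/n1 + 1/n2)
- AUC = Φ(d/√2)
- sensitivity = specificity = Φ(d/2) at the midpoint cut-off

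For 33 vs 33: d = 1.998 × √(2/33) = 0.492; AUC = Φ(0.348) = 0.636; sensitivity = specificity = Φ(0.246) = 0.597.

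| Assumed split | d at p = 0.05 | AUC | Sens = spec |
|---|---|---|---|
| I vs II, 33 vs 33 | 0.492 | 0.636 | about 60% |
| I vs II, 25 vs 25 | 0.569 | 0.656 | about 61% |
| I+II vs III, 67 vs 33 | 0.422 | 0.617 | about 58% |

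A marker that just reaches significance would misclassify about 4 in 10. Over a wider set of assumed splits with 80 to 100 evaluable (normal approximation), the AUC at p = 0.05 runs from about 0.61 to 0.67.

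**3. How the named contrast behaves.** Assumed: equal thirds (67 vs 33 when pooled), unit SD, illustrative d = 0.8, normal approximation, power = Φ(difference/SE − 1.96).

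- The SE for 67 vs 33 is √(1/67 + 1/33) = 0.213. For 33 vs 33 it is √(2/33) = 0.246.
- Marker following criterion 1 only (raised by 0.8 in both I and II): I+II vs III has power Φ(0.8/0.213 − 1.96), about 96%. Its AUC for stasis (I vs II) is 0.50.
- Marker following stasis only (raised by 0.8 in group I): the pooled difference is 0.8/2 = 0.40, with power Φ(0.40/0.213 − 1.96), about 47%. For I vs II, power is Φ(0.8/0.246 − 1.96), about 90%.

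The 47% ignores the extra spread from mixing I and II, so it is slightly generous.

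**4. Whether AUC estimation is feasible at this size.** Hanley-McNeil: SE² = [A(1−A) + (n1−1)(Q1−A²) + (n2−1)(Q2−A²)]/(n1·n2), with Q1 = A/(2−A) and Q2 = 2A²/(1+A).

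For A = 0.75 and 33 vs 33: Q1 = 0.600, Q2 = 0.643, SE² = (0.1875 + 1.200 + 2.571)/1089 = 0.00364. So SE = 0.060 and the 95% CI is about 0.63 to 0.87.

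| True AUC | Half-width, 33 vs 33 | Half-width, 25 vs 25 |
|---|---|---|
| 0.70 | 0.126 | 0.146 |
| 0.80 | 0.108 | 0.124 |

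**The case against.** The strongest reply is that this is a condensed article about an exploratory study. Section 2.10 introduces its comparison as basic and does not claim to be complete. An analysis plan that is not shown may contain ROC work. Screening candidates by group differences is a recognised early step, and the Discussion looks ahead to later trials. Much of this stands, and it limits the point to what the article describes. It does not remove the mismatch, because the article itself states both the diagnostic aim and the contrast that fails to isolate stasis. Being exploratory excuses the missing power calculation, but does not make a group-difference test answer a diagnostic question.

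A reader might infer two stronger claims, and the article supports neither.

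- That the plan cannot show discrimination at all. Mann-Whitney U divided by n1·n2 is the empirical AUC, and group means with SDs give d and, under normality, an AUC. The ingredients exist; the plan does not name or report the measure.
- That biomarkers and score are never analysed together. Groups I and II differ exactly on the score cut, so a three-group ANOVA or Kruskal-Wallis test does relate each biomarker to the dichotomised score. What is lost is the information above and below 9, and a dedicated I vs II estimate.

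It is also fair to say that any study of this size has modest discrimination at p = 0.05, and that an interval of 0.63 to 0.87 still includes 0.64. The AUC will not settle a marker's value here; it will show how uncertain that value is.

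**Conclusion.** The point holds in a limited form. The analysis described in 2.10 does not match the diagnostic aim: it names no discrimination measure, uses the score against the biomarkers only through the cut at 9, and names a contrast that divides on criterion 1 instead of blood stasis. The size is illustrative. Under an assumed 33 vs 33 split and equal-variance normality, a result at p = 0.05 corresponds to an AUC of about 0.64 and sensitivity and specificity of about 60%. All group splits and effect sizes are assumptions, since the article gives only the total of 100, and that target already allows for dropout.

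The documents do not support concluding that no discrimination analysis exists anywhere, or that the group comparisons must be dropped or the primary outcomes replaced. Recruitment and data collection are unaffected.

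**What to change.** In 2.10, add for each of the four biomarkers:

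1. The AUC with 95% CI for group I versus group II, that is, stasis-positive versus stasis-negative among participants meeting criterion 1.
2. A regression or rank correlation of the biomarker on the continuous blood stasis score, with transformation if the biomarker is skewed, so that the result does not hang on the cut at 9. Do this within groups I and II or adjust for criterion 1, because group III contributes only scores below 9 and differs on criterion 1.

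Keep the existing group comparisons as supportive. A model combining the biomarkers is optional; if one is fitted, report an optimism-corrected AUC.

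The cost is a little more analysis on data already to be collected. The intervals will be visibly wide, with a half-width of about 0.11 to 0.15 for AUC 0.70 to 0.80 at an assumed 25 to 33 per group. They should be presented as exploratory.

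### The stated aim is diagnostic, but the analyses in section 2.10 only test whether groups differ, and the named contrast is not defined by blood stasis

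*Protocol article*

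**What the plan says.** Section 2.1 (Study aims) describes the purpose as "designing a Korean medicine diagnostic technique for metabolic diseases with blood stasis", together with exploring treatment options and evaluating validity. Section 2.7.1 (Primary outcome) lists four blood markers which, on the strength of earlier studies, "are the candidate indicators that seem effective in diagnosing blood stasis"; the blood stasis questionnaire score is the other primary outcome. The Discussion says the study is "designed to investigate the effectiveness of the diagnosis index for metabolic diseases with blood stasis".

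Section 2.10 (Statistical analysis) sets out to "compare the difference in evaluation indicators of groups I and II (with circulatory disturbances) with that of group III (without circulatory disturbances) at visit 1". The tools are group summaries, chi-square and Fisher tests, t test and ANOVA or their rank-based counterparts, and ANCOVA where adjustment is needed. They are applied "To compare the intergroup differences for the obtained outcome value for each item", two-sided at 5%.

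Section 2.4.1 defines the groups. Criterion 1 is a low ankle-brachial index or a lipid pattern; criterion 2 is a blood stasis score of at least 9. Group I meets both, group II meets only criterion 1, and group III meets neither. Section 2.9 gives a recruitment target of 100 that allows for dropout, with no effect size, dropout figure or group split.

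**The concern.** A between-group test asks whether averages, ranks or proportions differ. A diagnostic aim asks how often a marker puts an individual on the right side of a line. With about 100 people, a marker can differ clearly on average while its distributions overlap so much that it classifies few individuals correctly. The article mentions no ROC curve, AUC, cut-off, sensitivity, specificity or predictive value, so none of the analyses it states is tied to the diagnostic aim.

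The named contrast adds a second mismatch. Everyone in groups I and II meets criterion 1 and nobody in group III does, while the blood stasis criterion is met in group I only. A difference between I and II together and III may therefore reflect vascular or lipid status rather than blood stasis. At stake is whether the results can carry a statement about a diagnostic marker for blood stasis, or only one about association.

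**Working it through.** The plan states no effect size or power, so there is no figure of its own to reproduce. The check asks how much discrimination a marker has when its group difference only just reaches p = 0.05.

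**Inputs from the article:** two-sided 5% (2.10); 100 participants as recruitment target (2.9).

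**Assumptions, not in the article:** all 100 evaluable; group splits as listed; normally distributed markers with equal SD in both groups, possibly after transformation.

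**Formulas**
- Smallest significant standardised difference: d = t(0.975, n1+n2−2) × √(1/n1 + 1/n2)
- AUC = Φ(d/√2)
- Sensitivity = specificity at the midpoint cut-off = Φ(d/2)
- Sensitivity at 90% specificity = 1 − Φ(1.2816 − d)

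**Results**

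| Split | d | AUC | Sens = spec at midpoint | Sens at 90% spec |
|---|---|---|---|---|
| 50 v 50 | 0.397 | 0.611 | 58% | 19% |
| 67 v 33 | 0.422 | 0.617 | 58% | 20% |
| 80 v 20 | 0.496 | 0.637 | 60% | 22% |
| 33 v 33 (one pair of groups) | 0.492 | 0.636 | 60% | 22% |

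For 67 v 33: √(1/67 + 1/33) = 0.2127; times 1.984 gives d = 0.422; Φ(0.422/1.414) = 0.617.

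**Sensitivity to dropout.** With 80 evaluable, the just-significant AUC is 0.624 (40 v 40), 0.630 (53 v 27) or 0.653 (64 v 16).

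**Check without the normal model.** For Mann-Whitney, the smallest significant AUC is about 0.5 + 1.96 × √((n1+n2+1)/(12·n1·n2)): 0.614 at 50 v 50, 0.621 at 67 v 33 and 0.640 at 33 v 33. These agree with the table.

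**For scale.** An AUC of 0.80 needs d = √2 × Φ⁻¹(0.80) = 1.19, more than twice any d in the table. At 67 v 33, a marker with a true AUC of 0.65 (d = 0.545, midpoint sensitivity and specificity about 61%) has about 73% power to reach significance.

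**What an AUC interval would show (Hanley-McNeil standard error).** At 67 v 33, an observed AUC of 0.617 has a 95% CI of about 0.50 to 0.73, and 0.80 has about 0.71 to 0.89. At 33 v 33, the half-width is 0.126 at AUC 0.70 (0.57 to 0.83) and 0.108 at AUC 0.80 (0.69 to 0.91).

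**Which contrast bears on blood stasis**

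| | Criterion 1 (ABI/lipids) | Criterion 2 (stasis score) |
|---|---|---|
| Group I | met | met |
| Group II | met | not met |
| Group III | not met | not met |

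I and II v III differs throughout on criterion 1 and only partly on criterion 2. I v II holds criterion 1 fixed and differs only on criterion 2.

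**The case against.** The strongest reply is that the study is exploratory, calls its markers candidates, and looks ahead to later trials. Comparing candidates between groups is a reasonable first screen, and the planned tests are valid for what they test. This stands, and it makes rewording the aim a proportionate remedy. It does not make a group test an answer to a diagnostic question. Estimating an AUC with an interval suits an exploratory study without a power calculation.

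A reader might infer that the study has no accuracy analysis at all and cannot answer its question. The article does not support that: it condenses a fuller protocol, a separate analysis plan may exist, and section 2.10 presents its comparison as a basic one, which does not claim to be complete. What stands is that the analyses it does state do not match the aim it states.

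A reader might also infer that p < 0.05 is the plan's rule for declaring a marker effective. No section says so. The 5% level is linked to no claim of effectiveness, and the remark in 2.7.1 that the markers seem effective describes earlier studies. Nor does the article define its diagnosis index as a composite of the four markers, so the lack of a combined model is no fault.

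Finally, an approximate AUC could be recovered from the group means and SDs, or from the Mann-Whitney U divided by n1 × n2. That is true and shows the repair is cheap. Neither conversion, nor an interval for it, is planned in the article.

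**Conclusion.** The concern holds as a mismatch between aim and stated analysis. The aim and Discussion are diagnostic; every inferential analysis in 2.10 is a between-group test, and the named contrast is set by ankle-brachial index and lipids. Under the assumptions above, a just-significant marker has an AUC of about 0.61 to 0.64 and detects roughly one case in five at 90% specificity. Allowing for 80 evaluable participants moves the upper end to about 0.65. The group splits and the equal-SD normal model are assumptions, but the conclusion is the same across the splits tried and in the rank-based check. These figures describe a result at the significance threshold, not the result to be expected. The point is that significance alone would not support a diagnostic claim, not that the plan commits itself to making one on that basis. Nothing is irrecoverable, but it should be settled before the data are analysed.

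**What to change.** In section 2.10, for the four blood markers:

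- Report the AUC with 95% CI, and sensitivity at a fixed specificity such as 90%, for group I v group II, where both groups meet criterion 1 and only the blood stasis criterion differs.
- Report the same for groups I and II v III, labelled as discrimination of circulatory disturbance.
- Keep the planned group tests as description.
- State that any diagnostic statement will rest on the AUC and its lower confidence limit.

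A model combining the four markers is optional.

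Alternatively, leave 2.10 as it is and reword section 2.1 and the Discussion so that they speak of the association of candidate markers with blood stasis.

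The cost is wording and a few hours of analysis on data already to be collected at visit 1. The downside is that the AUC intervals will be wide, about ±0.11 to ±0.13 at 33 v 33, and the published claim may look less favourable than a list of p-values.
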